### Interim analyses {21b}

There are no interim analyses planned.

### Methods for additional analyses (e.g., subgroup analyses) {20b}

The Pearson correlation analysis method was used to analyze the correlation between joint position perception errors and gait and plantar pressure parameters after adjusting for known or selected confounders.

### Methods in analysis to handle protocol non-adherence and any statistical methods to handle missing data {20c}

The intention-to-treat (ITT) paradigm was used to solve compliance problems, and patients who wanted to withdraw from the comparator group were included in the intervention group.

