### Trial design{8}

This trial is a single center, single-layer (the experimental group and the comparator group were randomly assigned in a 1:1 balanced manner), and the evaluator was blind.

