### Sample size {14}

Using the G Power 3.1.9.7 software, previous studies showed that between the proprioceptive training group and the comparator group, the effective amount of JPS joint position perception difference *d* = 0.97 [13]; According to power = 80%, alpha = 0.05, and *d* = 0.97, the required sample size *n* = 36 is calculated. Considering the loss of 10% sample size, 40 subjects are required.

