### Plans to promote participant retention and complete follow-up {18b}

We will use an intention-to-treat (ITT) analysis. A study participant is analyzed as belonging to whatever treatment group he/she was allocated, whether or not the treatment course was completed as intended.

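### The non-adherence rule places comparator patients who want to withdraw in the intervention group, against the plan's own intention-to-treat rule

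*Protocol article*

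**What the plan says.** Three sections of the protocol article deal with a patient who does not continue as allocated.

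- **Retention and follow-up {18b}:** the analysis is by intention to treat. "A study participant is analyzed as belonging to whatever treatment group he/she was allocated, whether or not the treatment course was completed as intended".
- **Non-adherence and missing data {20c}:** "The intention-to-treat (ITT) paradigm was used to solve compliance problems", and in the same sentence "patients who wanted to withdraw from the comparator group were included in the intervention group". There is no matching rule for patients who want to leave the intervention group.
- **Adverse event reporting and harms {22}:** patients who take up other rehabilitation, or who will not go on because they are recovering slowly, are to be removed. The section does not say whether this means from treatment, from follow-up or from the analysis.

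Patients are "randomly assigned in a 1:1 balanced manner" (Trial design {8}). The planned total is 40 (Sample size {14}).

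**The concern.** A comparator patient who wants to withdraw cannot be both analysed as allocated and counted in the intervention group. The second half of the {20c} sentence also undoes the principle named in its first half. Because the article states the rule outright, an unseen analysis plan could add detail but would not make the sentence correct.

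The movement goes one way and is chosen by the patient. Section {17a} says that patients and treating staff are not blinded, so comparator patients know that they lack the added training. Section {22} itself anticipates patients stopping because of slow recovery, so a link between the wish to withdraw and the outcome is plausible. If poor recoverers are moved, the bias goes against the training; if the movers would have done well anyway, it goes in its favour. The rule would affect every outcome, including the primary ones, and two patients are 10% of a 20-patient arm.

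**Working it through.** **1. The plan's own figure.** Inputs from Sample size {14}: d = 0.97, alpha 0.05, power 80%, 10% loss. Sidedness is not stated. A two-sided two-sample t-test (noncentral t) needs 17.70, so 18 per arm and 36 in total (power 80.7%). A one-sided test gives 28, which does not match. Inflating, 36 / 0.90 = 40. The plan's 36 and 40 reproduce and are not at issue. With 20 per arm and no loss, power is 84.8%.

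**2. Assumptions for the illustration.** The documents give no number of movers (k), no distance of movers from the average and no correlation with outcome. I take k = 2 and 4, 20 per arm, SD 1, one outcome and a two-sided t-test. This is simpler than the planned repeated-measures ANCOVA. Movers keep a comparator outcome but are counted in the intervention group, so the analysed groups become 22 v 18 or 24 v 16.

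**3. Moving unrelated to outcome.** The expected difference is 0.97 × 20/(20 + k):
- k = 2: 0.97 × 20/22 = 0.88
- k = 4: 0.97 × 20/24 = 0.81

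Simulation (50,000 trials per case) gives 0.88 and 0.81, with power 76% and 65%. With no true effect, rejection is 5.0% (k = 2) and 5.1% (k = 4).

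**4. Moving related to outcome, no true effect.** If the movers' mean lies m SD from average, the spurious difference is km/(20 + k) + km/(20 − k) = 40km/(400 − k²). For m = 1:
- k = 2: 80/396 = 0.20 SD
- k = 4: 160/384 = 0.42 SD

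In the simulation, the movers are the k comparator patients ranked highest on a score with correlation r to outcome (40,000 trials per case):

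| r | k = 2: bias (SD), type I error | k = 4: bias (SD), type I error |
|---|---|---|
| 0.3 | 0.10, 5.8% | 0.17, 8.0% |
| 0.5 | 0.17, 7.7% | 0.28, 13.3% |
| 0.8 | 0.26, 12.4% | 0.44, 27.4% |

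Check: the bias should be proportional to r, and perfect correlation gave 0.329 SD (k = 2) and 0.556 SD (k = 4). So 0.3 × 0.329 = 0.10, 0.8 × 0.329 = 0.26, 0.3 × 0.556 = 0.17 and 0.8 × 0.556 = 0.44, which agrees. With one mover, rejection is 5.4% to 6.9% over the same range of r.

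**5. Moving related to outcome, true d = 0.97, r = 0.5.** Power is 55% (k = 2) or 30% (k = 4) if movers have the worse outcomes, and 90% or 92% if they have the better ones.

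**6. The milder reading.** Suppose movers receive the added training, benefit in full and are analysed as randomised. The expected difference is then 0.97 × (20 − k)/20: 0.97 × 18/20 = 0.87 for k = 2, and 0.97 × 16/20 = 0.78 for k = 4.

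**The case against.** The strongest reply is that the clause may describe treatment and not analysis: patients dissatisfied with the comparator are offered the added training but are still analysed where they were randomised. The sentence opens with intention-to-treat, and the article's English is loose elsewhere. On that reading {18b} and {20c} are compatible and randomisation is intact. This stands as a possibility, and the contradiction should therefore be claimed only for the text as written. It is the less natural reading, because the section concerns methods of analysis and nothing in it mentions an offer of treatment. It would also leave the one-directional dilution in step 6.

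Three stronger inferences are tempting, and the documents do not support them:

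- **That type I error is necessarily inflated.** It is inflated only if moving is related to outcome. Otherwise it stays near 5% and the loss is in power.
- **That allocation is no longer 1:1.** Allocation stays as randomised; only the analysed group sizes change.
- **That the upper figures, such as 27%, estimate what will happen.** They need four movers and a correlation of 0.8, neither of which the documents give.

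It is also fair to object that rewriting {20c} alone would leave it in conflict with {22}, under which some of the same patients are removed. The fix has to cover both.

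**Conclusion.** The point holds for the text as written: {20c} contradicts {18b} and itself, and followed literally it replaces the randomised comparison with one that is partly self-selected, in one direction. That conclusion rests on the wording and needs no simulation.

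The size is illustrative. For 2 to 4 movers out of 20, it runs from a loss of power with no inflation of type I error (step 3) to a bias under no true effect of 0.10 to 0.44 SD. That is about 10% to 45% of the planned 0.97 (0.10/0.97 and 0.44/0.97). The direction cannot be known in advance, so a reader could not correct for it afterwards. The sample size is unaffected. The sentence must be corrected before analysis.

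**What to change.** In {20c}, replace the clause on withdrawing comparator patients with: *All randomised patients are analysed in the arm to which they were allocated; any change of training is recorded and reported as non-adherence.*

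Then reconcile {18b}, {20c} and {22}, so that patients who stop or receive other rehabilitation are neither moved to another arm nor removed from the analysis. Their already scheduled 6- and 12-week assessments should be used where obtained.

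This concerns analysis grouping only. Whether such patients may receive the added training is for the investigators to settle and state. If the clause was meant as an offer of training, it should say so and be kept separate from the analysis rule.

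Cost: edits to two sections ({20c} and {22}), and completing planned assessments in patients who would otherwise be dropped. The target stays at 36, inflated to 40.

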### Plans to give access to the full protocol, participant-level data and statistical code {31c}

The datasets analyzed during the current study and statistical code are available from the corresponding author on reasonable request, as is the full protocol.

## Oversight and monitoring

### Data monitoring {21a}

Because the intervention protocol is of low risk, a data monitoring committee is not necessary in this trial. The research team is in charge of reporting immediately to the leading researcher about any accident.

### Adverse event reporting and harms {22}

Adverse reactions include ligament rupture again, patients receiving other rehabilitation intervention programs midway, or patients unwilling to continue training because of slow functional recovery, patients will be rejected and the project will be terminated.

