### Intervention description {11a}

The comparator group receives routine rehabilitation training after surgery, which is the first option for ACLR (Table 1). The intervention group program adds proprioceptive training on the basis of routine rehabilitation training, three times a week, 20 min each time. The intervention will be conducted on the first day after surgery.

**Table 1 Tab1:** The routine rehabilitation training

Focus on functional training
1. Jogging training, 10 min
2. Single-leg squat exercise, three series of 10 repetitions
3. Jump training, three series of 10 repetitions
4. Strength exercise of quadriceps femoris, 70–80% 1RM (1 repetition maximum), two series of 8–12 repetitions

Proprioceptive program: ① The therapist ties the mobile phone with the software to measure the flexion angle of the joint above the patient’s lower leg. Participants take a supine position with eyes closed and the therapist passively flexes the knee joint on the operative side of the participants to any angle. Participants will be asked to repeatedly bend to this angle, three series of 10 repetitions, per angle. Three angles are randomly set(5 degrees of error); ② The therapist ties the mobile phone with the software to measure the flexion angle of the joint above the patient’s lower leg. Participants take a sitting position with eyes closed. Patients actively extend the knee joint to any angle. Participants will be asked to repeatedly bend to this angle, three series of 10 repetitions, per angle. Three angles are randomly set (5 degrees of error).

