### Criteria for discontinuing or modifying allocated interventions {11b}

The intervention will be discontinued when there is unbearable knee pain or ligament rupture again and the patient’s exercise frequency is less than 80%.

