### Strategies to improve adherence to interventions {11c}

All participants will be pulled into a WeChat group and they can ask questions directly. Participants need to clock in one time every week and will be reminded monthly about their rehabilitation plan by phone.

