### Relevant concomitant care permitted or prohibited during the trial {11d}

In order to make the patients receive the same rehabilitation as possible within 3 months after surgery, the early rehabilitation training is printed and taken home after discharge (Table 2). Participants will be informed that rehabilitation interventions, other than those that will be received during the period of the study, will not be allowed.

**Table 2 Tab2:** The early rehabilitation training

**Stage**	The early rehabilitation training
0–3 weeks	1. Using fascial knife to reduce swelling, 5 min 2. Moving patella, 2 series of 10 repetitions 3. Flexing knee joint (0–90°), three series of 10 repetitions 4. Straightening the knee joint to the level of the healthy side 5. Straight leg raising (SLR), three sets of 10 reps 6. Glute bridge, three sets of 10 reps 7. Walking with crutches
3–6 weeks	Besides the above scheme: 1. Increasing the flexion angle of the knee joint to achieve a full range of activities in 6 weeks 2. Gradually reducing the use of crutches, and do not use braces and crutches when walking for 6 weeks 3. The resistance can be increased when the straight leg is raised 4. Step up exercise 5. Intensive exercise of vastus medialis
6–12 weeks	If the above actions have been completed easily, go to the next step (pay attention to the training intensity in 8–10 weeks, and the ligament strength in the remodeling period is insufficient), and focus on flexibility training: 1. Squat training against the wall 2. Abduction training of muscles around the hip 3. Power bicycle training 4. Stair down training (after 10 weeks) 5. Seat squatting training

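### The definition of adverse reactions in Adverse event reporting and harms {22} counts a protocol deviation and a withdrawal as harms and does not list knee pain, stiffness or infection, all named elsewhere in the article

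*Protocol article*

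**What the plan says.** All references are to the protocol article.

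- **Adverse event reporting and harms {22}** gives the only description of harms: "Adverse reactions include ligament rupture again, patients receiving other rehabilitation intervention programs midway, or patients unwilling to continue training because of slow functional recovery". The same sentence then states the consequence: "patients will be rejected and the project will be terminated".
- **Relevant concomitant care {11d}** tells participants that rehabilitation interventions "other than those that will be received during the period of the study, will not be allowed".
- **Criteria for discontinuing {11b}**: "The intervention will be discontinued when there is unbearable knee pain or ligament rupture again".
- **Exclusion criteria** name knee stiffness and infection as examples of postoperative complications. The Abstract places consent and the baseline assessment within the two weeks before surgery, and the training on the first day after it.
- **Data monitoring {21a}** decides against a monitoring committee because the intervention is judged low risk. It gives one reporting route: "The research team is in charge of reporting immediately to the leading researcher about any accident".
- **Strategies to improve adherence {11c}**, which applies to all participants: "Participants need to clock in one time every week and will be reminded monthly about their rehabilitation plan by phone". The Abstract adds assessments at 6 and 12 weeks.
- **Plans to promote participant retention {18b}** commits to intention-to-treat: participants are analysed in the allocated group whether or not they completed treatment.

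**The concern.** A harms section has to tell whoever records events what counts as one. This one puts two matters of conduct under the label of adverse reaction and leaves out complications that the article mentions elsewhere.

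Three things are at stake:

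1. A patient who seeks extra rehabilitation, or who stops because progress is slow, would be recorded as having had an adverse reaction without any injury.
2. A painful, stiff or infected knee might not be recorded as a harm. For stiffness and infection there is a further route to loss. They are exclusion criteria that can only be met after surgery, hence after consent and baseline, so a case arising during the trial could be handled as ineligibility instead.
3. The judgement that the intervention is low risk, on which the absence of a monitoring committee rests, could not be checked against records kept this way.

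**Working it through.** The article gives no figure on harms, so there is none to reproduce. The check is mainly a comparison of sections.

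**Step 1. What the listed items are.**

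| Item listed in {22} | How the article treats it elsewhere | Nature |
|---|---|---|
| Re-rupture | Reason to discontinue, {11b} | Injury |
| Outside rehabilitation | Prohibited, {11d} | Protocol deviation |
| Unwilling to continue because recovery is slow | Non-completion of treatment, which {18b} covers | Withdrawal or non-adherence |

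Two of the three are not harms.

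**Step 2. Complications named anywhere in the article.**

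| Complication | Where named | Listed in {22}? |
|---|---|---|
| Re-rupture | {11b}, {22} | Yes |
| Unbearable knee pain | {11b} | No |
| Knee stiffness | Exclusion criteria | No |
| Infection | Exclusion criteria | No |

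Three of the four are not listed. The case of pain is the clearest, because {11b} names pain and re-rupture together and {22} carries over only re-rupture.

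**Step 3. Consequence for the patient.** Under {22} a patient with any listed item is rejected. Under {11b} re-rupture ends the intervention. Under {18b} a patient who does not complete treatment is still analysed as allocated. If rejection means removal from the trial or its analysis, {22} contradicts {18b}. It is also unclear whether the project that is terminated is the patient's participation or the trial.

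**Step 4. Can the distortion be sized?** Suppose there are 20 patients per arm (40 in total, allocated 1:1), a true harm rate h, and a rate d of the two conduct items, with h and d independent. Both rates are assumed; the article gives neither. The expected number of patients with an adverse reaction as defined is 20 × [1 − (1 − h)(1 − d)].

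- h = 10%, d = 5%: 20 × (1 − 0.90 × 0.95) = 2.9.
- h = 10%, d = 20%: 20 × (1 − 0.90 × 0.80) = 5.6.

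With the same true harm rate of 10% in both arms:

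| Conduct rate, intervention vs comparator | Expected count, intervention vs comparator |
|---|---|
| 5% vs 5% | 2.9 vs 2.9 |
| 5% vs 20% | 2.9 vs 5.6 |
| 20% vs 5% | 5.6 vs 2.9 |

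With h = 5% the two conduct rates give 1.95 and 4.8. With h = 20% they give 4.8 and 7.2. Conduct alone can therefore create a gap of two to three patients, in either direction, or none. The article does not say which case applies.

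**The case against.** **The list is open.** The sentence says what adverse reactions include, so other events are not barred. This stands as far as it goes, and a careful recorder could still note pain. But examples of which two in three are not harms misdirect the reader, and an open list does not cure the wrong classification of those two.

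**The sentence may be a mislabelled list of withdrawal triggers.** Read with its closing clause, it can be taken that way. The reading is fair. On it, however, the harms section contains no definition of harm at all, and the conflict with {18b} becomes sharper.

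**An article leaves forms and schedules to the full protocol.** This stands. The absence of a case report form or an event checklist is not raised as a fault. What is raised is a definition that the article does state.

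**A stronger reading that the text does not support.** A reader might infer that harm reporting depends on contacts far more frequent in one arm. The intervention group "adds proprioceptive training on the basis of routine rehabilitation training, three times a week, 20 min each time", and in the first exercise "the therapist passively flexes the knee joint on the operative side of the participants to any angle". The document does not bear the inference out:

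- No section ties harm capture to the training sessions; {21a} makes the research team as a whole responsible.
- The printed take-home programme in {11d} is the early rehabilitation of Table 2, and nothing limits it to one arm.
- The article does not say whether the comparator's routine training (Table 1) is supervised, nor for how many weeks the added sessions run.
- The follow-up contacts that are stated (weekly clock-in, monthly call, 6- and 12-week assessments) apply to everyone.

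Unequal detection is possible, since patients and implementers are not blinded, but it is not shown.

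**Conclusion.** The definition in {22} is wrong as written and should be changed. This rests on the text alone: two of three listed items are a deviation and a withdrawal, and three of the four complications named in the article are not listed.

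The consequence is conditional. Counts built on this definition would mix conduct with injury and could miss named complications, so counts by arm could be distorted. The figures in Step 4 rest on assumed rates and show only that a gap can arise in either direction or not at all.

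A reader might go further and conclude that the comparison of harms will be wrong. That does not follow. The article plans no between-arm comparison of harms: they are not among the outcomes in {12}, and {20a} names no such analysis. The net direction of any bias is unknown.

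Nor would a correct definition let so small a trial establish low risk. With no events in 20 patients, the one-sided 95% upper limit for the true rate is 1 − 0.05^(1/20) = 13.9%. It would make the records fit to be read for that purpose.

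**What to change.** 1. Reword {22} so that adverse events are untoward medical events after surgery in either arm, whether or not attributed to the training. Name re-rupture, knee pain, stiffness and infection as events to record.
2. Move outside rehabilitation to protocol deviations, and unwillingness to continue to withdrawals.
3. Record events with the same short set of questions in both arms at contacts already planned for all participants: the weekly clock-in, the monthly call, and the 6- and 12-week assessments.
4. Reconcile the rejection and termination clause in {22} with {11b}, with the exclusion criteria, and with the intention-to-treat statement in {18b}. Say what is terminated, and how a patient who develops a listed complication after enrolment is followed and analysed. Which clinical rule applies is for the investigators; the sections need to agree.

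The cost is the rewording of one section, a few minutes per contact, and higher reported event counts, which should be expected and explained. The sample size of 40 is unaffected.

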#### Exclusion criteria

Insufficient range of motionPostoperative complications such as knee stiffness and infectionAnterior cruciate ligament rupture for more than 1 monthOther diseases affecting gait: chronic ankle instability, scoliosis, etc.Accompanied by injury of articular cartilage and other ligaments

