## Assignment of interventions: blinding

### Who will be blinded {17a}

Because the implementers and patients of the proprioceptive training group and the conventional group can clearly observe; Therefore, the blind method of this study is only blind for the evaluators of outcome indicators and data analysts. Data collection and analysis shall be conducted independently by researchers who do not participate in the trial.

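### Patients are to be rejected for events that happen after allocation, which conflicts with the promise to analyse everyone as allocated

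*Protocol article*

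**What the plan says.** All references are to the protocol article.

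- **Adverse event reporting and harms {22}** opens its list with "Adverse reactions include ligament rupture again, patients receiving other rehabilitation intervention programs midway" and closes it with "patients unwilling to continue training because of slow functional recovery, patients will be rejected and the project will be terminated".
- **Exclusion criteria** include postoperative "complications such as knee stiffness" and infection.
- **Intervention description {11a}** fixes the start of training: "The intervention will be conducted on the first day after surgery". The Abstract places consent and baseline assessment within the two weeks before surgery.
- **Criteria for discontinuing {11b}** deals separately with stopping training: "The intervention will be discontinued when there is unbearable knee pain or ligament rupture again", together with an adherence threshold of 80%.
- **Concomitant care {11d}** bars rehabilitation "other than those that will be received during the period of the study, will not be allowed".
- **Retention and follow-up {18b}** commits to intention-to-treat: "A study participant is analyzed as belonging to whatever treatment group he/she was allocated", regardless of whether treatment was completed.
- **Blinding {17a}** limits blinding to outcome assessors and analysts, giving this reason: "Because the implementers and patients of the proprioceptive training group and the conventional group can clearly observe".

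**The concern.** The harms section treats non-compliance and poor progress as grounds for rejecting a patient. The follow-up section says the same kind of non-compliance must not change who is analysed. Both cannot be followed if a rejected patient is no longer assessed, and nothing in the article says that rejected patients still attend at weeks 6 and 12.

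The reasons for rejection matter. Stopping because recovery is slow, or looking for help elsewhere, is close to what the trial measures. Patients and therapists know the arm, and only one arm carries the added sessions, so who is rejected can depend on both arm and progress. Blinded assessment does not protect against that. Losses mainly from the intervention arm would flatter the training; losses mainly from the comparator arm would hide a real effect. Visits that were never made cannot be restored at analysis.

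Listing stiffness and infection as exclusions has a second effect: patients with these complications could drop out of the comparison of harms.

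**Working it through.** **Step 1. Order of events.** Consent and baseline come before surgery. The envelope is opened once inclusion is confirmed (Implementation {16c}); no date relative to surgery is given. Allocated training starts on day 1 after surgery, so allocation can be no later than that.

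| Event | Stated under | When it can occur |
|---|---|---|
| Re-rupture | Harms {22}; also {11b} | After surgery and allocation |
| Outside rehabilitation midway | Harms {22} | During training, so after allocation |
| Unwilling to continue, slow recovery | Harms {22} | During training, so after allocation |
| Postoperative stiffness, infection | Exclusion criteria | After surgery; in practice after day 1 |

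**Step 2. Meaning of rejection.** Section {11b} already covers stopping training and says that the *intervention* is discontinued. Section {22} says that *patients* are rejected. Rejecting someone who has already declined to train adds nothing unless it removes that person from the trial. Removal is an inference, but it is the reading that gives the sentence work to do.

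**Step 3. The plan's own sample size.** Inputs from Sample size {14}: d = 0.97, power 80%, alpha 0.05 (taken as two-sided), 10% loss. Two-sample t-test, noncentrality d·√(n/2), 2n − 2 degrees of freedom:

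- 17 per arm gives 78.3%; 18 per arm gives 80.7%, so 36 in total.
- 36 / (1 − 0.10) = 40.

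The stated 36 and 40 reproduce. Power is 84.8% with 40 analysed, 80.7% with 36 and 75.6% with 32. The allowance is 40 − 36 = 4 patients for losses of every kind.

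**Step 4. Size of a selective loss.** The documents give no removal rates, so these are assumptions: 20 per arm, normal outcome with SD 1 and higher values better, the k lowest patients removed on a score correlated r with outcome, unadjusted two-sided t-test at 0.05, by simulation (200,000 runs under the null).

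| Removed (one arm v other) | r | Bias (SD) | Type I error |
|---|---|---|---|
| 2 v 1 | 0.5 | 0.04 | 5.6% |
| 2 v 0 | 0.5 | 0.09 | 6.2% |
| 3 v 1 | 0.8 | 0.13 | 8.4% |
| 4 v 0 | 0.8 | 0.27 | 13.7% |
| 2 v 2 | 0.5 | 0 | 5.6% |
| 2 v 2 | 0.8 | 0 | 6.6% |

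A large-sample check: removing the lowest fraction f shifts the arm mean by r·φ(z)/(1 − f), where z is the normal quantile at f. The ratio φ(z)/(1 − f) is 0.195 at f = 0.10 and 0.35 at f = 0.20.

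- 2 of 20 at r = 0.5: 0.5 × 0.195 = 0.10, against 0.09 simulated.
- 4 of 20 at r = 0.8: 0.8 × 0.35 = 0.28, against 0.27 simulated.

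**Step 5. If d = 0.97 is true** (same model):

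- Comparator loses 2 at r = 0.5: estimate 0.97 − 0.09 = 0.88; power falls from 85% to 76%.
- Comparator loses 4 at r = 0.8: estimate 0.97 − 0.27 = 0.70; power 58%.
- Intervention loses 2 at r = 0.5: estimate 0.97 + 0.09 = 1.06; power 89%.

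**The case against.** - **Rejected is never defined.** The sentence is loosely worded, sits under harms and does not mention follow-up or the analysis set. It cannot sensibly mean that the whole trial ends when one patient stops, so it may mean only that this patient's programme ends. Section {18b}, which does govern the analysis, would then prevail. This is possible, but Step 2 counts against it, and if both readings are open, site staff may follow either.
- **A condensed article may leave follow-up of withdrawn patients to the full protocol.** That is fair as far as silence goes. The point, however, rests on rules the article does state and that pull against each other.
- **Section {20c} moves comparator patients who want to withdraw into the intervention group.** This weakens the comparator-only scenarios in Step 5 where the cause is quitting; they could still arise through re-rupture or outside rehabilitation. That rule is a separate departure from intention-to-treat, and this point does not depend on it.
- **The figures rest on assumptions and are small near the planned 10% loss.** This stands. The planned efficacy analysis is also a repeated-measures ANCOVA, so the t-test results indicate scale only.
- **Patients with re-rupture may be unable to do the tests anyway.** This also stands. The main gain is for patients who stop training or go elsewhere.

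**Conclusion.** The concern holds and should be fixed. The harms section and the exclusion criteria remove patients for events after allocation, in conflict with the stated intention-to-treat rule. That rejection means leaving the trial is an inference, though the stronger reading.

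The damage depends on how many are lost, from which arm and for what reason, none of which the documents give. Under the assumptions above, a null comparison shifts by 0.04 to 0.27 SD when losses are unequal, with type I error from just under 6% to about 14%. The upper end is close to a worst case. Equal losses cause no mean bias and mainly cost power. The trial is not invalidated, but an avoidable rule puts its main comparison at risk.

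**What to change.** 1. **Harms {22}.** Replace the rejection and termination clause with: *These events may end the training. The patient stays in the 6- and 12-week assessments and is analysed as randomised. Any test that is unsafe after re-rupture is recorded as not done, with the reason.*
2. **Exclusion criteria.** Move postoperative stiffness and infection to adverse events, recorded by arm.
3. **Discontinuation {11b}.** Add that discontinuation ends training and not follow-up. This section is already limited to the intervention, so the addition is only for clarity.

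The cost is these wording changes and recalling patients who stopped training to the two visits already scheduled: 2 × 2 = 4 visits if two stop, 4 × 2 = 8 if four stop. Some isokinetic or gait data will still be missing after re-rupture or infection, but with a recorded reason. The reassignment rule in {20c} needs its own correction before the intention-to-treat statement is fully consistent.
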